### Multi-omics quality control and reproducibility

2.8

For metabolomics and other omics assays, samples will be randomized across analytical batches. Pooled QC samples generated by mixing aliquots from study samples, procedural blanks, and internal standards will be included to monitor analytical stability and contamination. Repeated freeze–thaw cycles will be avoided. Features with high missingness or poor reproducibility in QC samples will be excluded according to prespecified thresholds, such as missingness exceeding 20–30% or QC coefficient of variation > 30%, depending on the omics platform. Batch effects will be evaluated and corrected using appropriate methods, such as QC-based signal correction or ComBat where applicable. Multiple testing will be controlled using the Benjamini-Hochberg false discovery rate. Candidate biomarkers identified from discovery analyses will be prioritized for validation using targeted assays or cross-platform confirmation where feasible.

### Ethics and data management

2.9

This study protocol was reviewed and approved by the Ethics Committee of Union Hospital, Tongji Medical College, Huazhong University of Science and Technology (approval number 2023–0525). All participants provided written informed consent before enrollment. The informed-consent process covered repeated questionnaire surveys, health assessments, biospecimen collection, long-term biospecimen storage, and future secondary analyses related to the approved research scope.

To protect participant privacy, each participant was assigned a unique study identification number. Biospecimens and research data were labeled and managed using study IDs rather than directly identifiable personal information. Personally identifiable information was stored separately from analytical datasets and was accessible only to authorized study personnel. Electronic data were stored in password-protected databases with restricted access, and paper documents were kept in secure locations. Data checking, cleaning, and analysis were performed using de-identified datasets.

Because this study involves blood, urine, stool, biobanking, microbiome profiling, metabolomics, and other potential omics analyses, additional measures were implemented to protect sensitive biological and omics-related information. Access to biospecimens and omics datasets will be restricted to authorized investigators and used only for ethically approved research purposes. Biospecimens will be stored in the study biobank at −80 °C according to institutional regulations and the approved consent scope. Any future secondary use beyond the current approved research scope will require additional ethical approval where applicable.

Clinically relevant abnormal findings identified during routine health assessments or laboratory examinations will be communicated to participants, who will be advised to seek further medical evaluation when necessary. De-identified data and analysis code may be made available from the corresponding author upon reasonable request, subject to ethical approval, participant privacy protection, and institutional data-sharing policies.

### Statistical analysis

2.10

Descriptive statistics will be used to summarize demographic characteristics, lifestyle factors, dietary variables, biomarker-based micronutrient profiles, and cardiometabolic risk factors. Continuous variables will be presented as means ± standard deviations or medians with interquartile ranges, depending on their distributions. Categorical variables will be summarized as numbers and percentages.

For single-exposure analyses, linear mixed-effects (LME) models will be used to evaluate associations between individual biomarker-based micronutrient levels and continuous cardiometabolic outcomes. The primary LME models will include a participant-specific random intercept to account for within-subject correlations across repeated measurements over time. Fixed effects will include potential confounders selected based on prior evidence, clinical relevance, and directed acyclic graph considerations, such as age, sex, ethnicity, education, smoking status, alcohol consumption, physical activity, total energy intake, season, medication use, and outcome-specific baseline health conditions. Random slopes for visit or time will not be included in the primary models because the limited number of repeated visits may reduce model stability and lead to convergence problems. However, models including random slopes will be evaluated in sensitivity analyses when convergence and model-fit indices support their use. For binary cardiometabolic outcomes, such as hypertension, dyslipidemia, or impaired glucose metabolism, mixed-effects logistic regression models will be used.

For mixture analyses, weighted quantile sum regression (WQS regression) will first be used to evaluate the overall joint association of micronutrient mixtures with cardiometabolic risk factors and to identify components that contribute most strongly to the mixture association. Because associations between micronutrients and outcomes may be non-linear, and because complex interactions may exist among mixture components, Bayesian kernel machine regression (BKMR) will also be applied as an exploratory approach to assess potential non-linear exposure-response relationships and high-dimensional interactions. For pairwise interactions with biological plausibility or *a priori* hypotheses, product terms will be included in mixed-effects models to evaluate interactions on the multiplicative scale. For binary cardiometabolic outcomes, such as hypertension, dyslipidemia, or impaired glucose metabolism, additive interactions will be further assessed using the relative excess risk due to interaction (RERI), attributable proportion due to interaction (AP), and synergy index (S) when sample size and model stability permit.

For multi-omics analyses, raw data will be preprocessed using platform-specific pipelines, including quality filtering, normalization, transformation, scaling, and batch-effect assessment or correction where appropriate. Omics features with excessive missingness or poor reproducibility in quality-control samples will be excluded according to prespecified criteria. Exploratory feature discovery will be performed using mixed-effects models or other appropriate methods that account for repeated measurements. Dimension-reduction or classification approaches, such as orthogonal partial least-squares-discriminant analysis (OPLS-DA), may be used as supplementary exploratory tools rather than as the primary basis for statistical inference. For omics features associated with biomarker-based micronutrient profiles or cardiometabolic risk factors, pathway enrichment analyses will be conducted to identify potentially perturbed biological pathways.

Mediation analyses will be conducted only when a plausible temporal and biological exposure-mediator-outcome sequence exists. Candidate mediators may include selected metabolites, microbiome features, inflammatory markers, oxidative-stress biomarkers, or other omics-derived features. These analyses will be considered exploratory because of the observational design and the complexity of repeated-measure data. The direct and indirect associations between micronutrient profiles and cardiometabolic risk factors through candidate biomarkers will be estimated using appropriate mediation models, with cautious interpretation regarding causality.

For analyses involving multiple exposures, outcomes, or high-dimensional omics features, multiple testing will be controlled using the Benjamini-Hochberg false discovery rate (FDR) where appropriate. Model stability will be assessed using internal validation procedures, such as repeated training-validation splits, bootstrapping, or sensitivity analyses with alternative model specifications, depending on the analytical method. Missing data and unbalanced repeated measurements will be handled primarily within mixed-effects models under the missing-at-random (MAR) assumption. The primary analyses will include all available person-visits rather than restricting analyses to participants with complete data from all four visits. For subsequent analytical manuscripts based on specific research questions, the proportion and pattern of missing data will be summarized for major exposures, outcomes, and covariates. Sensitivity analyses may include complete-case analyses, alternative covariate adjustment sets, exclusion of influential observations, multiple imputation for missing covariates, or inverse probability weighting to evaluate the influence of missing data and attrition, depending on the missing-data pattern, sample size, and model stability. Given the exploratory nature of the study, mixture modeling, non-linear analyses, interaction analyses, multi-omics discovery, and mediation analyses will be interpreted as hypothesis-generating rather than confirmatory.

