## Introduction

1

Cardiometabolic diseases, including cardiovascular diseases and diabetes, are leading contributors to morbidity and mortality among middle-aged and older adults (1, 2). Cardiometabolic diseases are driven by a constellation of interconnected cardiometabolic risk factors (CRFs), mainly including obesity, hypertension, dyslipidemia, and hyperglycemia (3). These risk factors not only increase individual susceptibility to adverse cardiovascular events but also impose a significant economic and societal burden on healthcare systems worldwide (4). Therefore, early identification and prevention of CRFs are critical for the control and management of cardiometabolic diseases epidemic, particularly among middle-aged and older populations (5, 6).

Micronutrients, including vitamins and minerals, are essential nutrients required in small quantities to support nearly all physiological functions (7–9). Numerous studies have reported associations between micronutrient and CRFs, but with mixed findings. A meta-analysis showed that higher levels of vitamin D were associated with a significant improvement in lipid profiles and reduction in systolic blood pressure, which were hallmarks of cardiovascular disease (10). Similarly, magnesium and zinc intake has been inversely associated with hyperglycemia, dyslipidemia, hypertension, and markers of inflammation, partly because of their potent antioxidant and anti-inflammatory properties (11, 12). Whereas high iron has been related to increased risks of insulin resistance and type 2 diabetes via introducing oxidative stress and endothelial dysfunction (13, 14). Moreover, for certain micronutrients, such as molybdenum and copper, their associations with CRFs are still largely unclear (15). In addition, previous studies have been constrained by neglecting the joint effects or interactions between different micronutrients on CRFs, inadequate adjustment for important confounders (e.g., chronic diseases or symptoms, dietary habits, and living or working environments), and/or crude exposure assessment that did not account for temporal variability in biomarker-based micronutrient profiles.

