### Micronutrients measurements

2.6

Micronutrients consist of vitamins and minerals that are crucial for the body’s proper functioning, yet required only in small quantities. Vitamins include fat-soluble types (A, D2, D3, E, K1) and water-soluble types (C, B1, B2, B3, B5, B6, B7, B9, B12), while minerals are divided into major essential minerals (Ca, K, Na, Cl, Mg, P), essential trace elements (Fe, Zn, Cu, Mn, Se, Co, Mo, Cr, I) and selected nutrition-related and environmentally relevant trace elements (Ni, V).

Vitamins were accurately measured by using high-performance liquid chromatography (HPLC) and liquid chromatography–tandem mass spectrometry (LC–MS/MS) (28, 29). For minerals, techniques including atomic absorption spectroscopy and inductively coupled plasma mass spectrometry (ICP-MS) were utilized to determine the accurate concentration in biological samples (30).

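### WQS regression is given the overall joint association, but a standard WQS index covers one direction only, and the background reports opposing directions within glucose metabolism

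*Protocol article*

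**What the plan says.** The Statistical analysis section (2.10) puts WQS first among the mixture methods. It states that "weighted quantile sum regression (WQS regression) will first be used to evaluate the overall joint association of micronutrient mixtures with cardiometabolic risk factors" and adds a second task, "to identify components that contribute most strongly to the mixture association". BKMR follows as an exploratory method for non-linearity and interactions. The same section treats all mixture modelling as generating hypotheses, not confirming them.

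The Introduction gives the expected directions:
- Vitamin D: "higher levels of vitamin D were associated with a significant improvement in lipid profiles and reduction in systolic blood pressure".
- Magnesium and zinc: "magnesium and zinc intake has been inversely associated with hyperglycemia, dyslipidemia, hypertension, and markers of inflammation".
- Iron: "high iron has been related to increased risks of insulin resistance and type 2 diabetes".
- Molybdenum and copper: "their associations with CRFs are still largely unclear".

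Section 2.6 (Micronutrients measurements) lists all of these among the analytes. Vitamin D appears as D2 and D3, magnesium is among the major minerals, and the rest are under "essential trace elements (Fe, Zn, Cu, Mn, Se, Co, Mo, Cr, I"). Section 2.7 makes glucose metabolism one of the primary outcome domains.

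**The concern.** A standard WQS index is a weighted sum of quantile scores. Its weights are non-negative and sum to one, and they are trained towards one chosen direction. Components associated with the outcome in the other direction receive weights near zero. With opposing components, the index therefore describes one side of the mixture, whereas the net joint association is the sum of both sides.

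The article makes this index the first-line answer to the joint part of aim 1 and also uses it to rank contributors. Two things could go wrong. A one-direction index could be reported as the joint association when the net association is small or absent. And a ranking from a single fit would pass over components that act the other way.

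**Working it through.** The article has no figure of its own on this point. Its one calculated number, the minimum sample size of 180, comes from a repeated-measures analysis of variance and does not enter here.

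**Step 1: is opposition within one outcome domain actually stated?**

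| Component | Direction in the Introduction | Outcomes named |
|---|---|---|
| Vitamin D | favourable | lipids, systolic blood pressure |
| Magnesium, zinc | inverse | hyperglycemia, dyslipidemia, hypertension, inflammation |
| Iron (high) | adverse | insulin resistance, type 2 diabetes |
| Molybdenum, copper | unclear | CRFs in general |

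The overlap with opposite signs is glucose metabolism: magnesium and zinc against iron. No opposing pair is given for adiposity, blood pressure or lipids.

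**Step 2: mixture size.** Section 2.6 lists 5 + 9 = 14 vitamins and 6 + 9 + 2 = 17 minerals and trace elements, 31 in all.

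**Step 3: the two targets.** With coefficient b_j per quartile step, the net joint effect is the sum of all b_j. A positive index can draw only on components with b_j > 0, and a negative index only on those with b_j < 0. Two components at +0.15 and two at -0.15 give a net of 2 × 0.15 - 2 × 0.15 = 0. One up and three down gives 0.15 - 0.45 = -0.30.

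**Step 4: simulation with 31 components.** Assumptions: quartile scores, active effects of ±0.15 residual SD per quartile step, 712 independent rows, weights bootstrapped in a 40% training set, slope estimated freely in the other 60%, 100 runs per setting (Monte Carlo SE at most √(0.25/100) = 5 percentage points). Percentages are the share of runs with a significant slope.

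| Active components | Correlation | True net | Positive index | Negative index | Unconstrained sum |
|---|---|---|---|---|---|
| 2 up, 2 down | 0 | 0.00 | +0.48 (78%) | -0.52 (82%) | -0.02 |
| 2 up, 2 down | 0.3 | 0.00 | +0.12 (46%) | -0.12 (40%) | 0.00 |
| 1 up, 3 down | 0 | -0.30 | +0.28 (39%) | -0.67 (97%) | -0.29 |
| 1 up, 3 down | 0.3 | -0.30 | -0.11 (36%) | -0.35 (100%) | -0.29 |
| 4 up | 0 | 0.60 | +0.84 (100%) | +0.02 (6%) | 0.60 |
| 4 up | 0.3 | 0.60 | +0.62 (100%) | +0.34 (100%) | 0.59 |

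The unconstrained sum tracks the true net in every row. WQS comes close to it when components are correlated and the index direction matches the dominant sign (rows 4 and 6). With 2 up and 2 down, the index does not recover the one-direction sum of 0.30 exactly either: it gives 0.48 without correlation and 0.12 with it.

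With 205 rows, the number of participants, instead of 712, the 2-up, 2-down rates fall to 24% and 16% (correlation 0) and to 7% and 6% (correlation 0.3).

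**Step 5: sensitivity to effect size.** Here three components have -0.15 and two have +0.225, so the net is -0.45 + 0.45 = 0. There are again 712 independent rows.

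| Components | Effect scale | Correlation | Positive index significant | Negative index significant |
|---|---|---|---|---|
| 10 | full | 0.3 | 96–97% | 81–85% |
| 10 | two thirds | 0.3 | 67% | 44% |
| 10 | one third | 0.3 | 12% | 9% |
| 31 | full | 0.3 | 91% | 59% |
| 31 | half | 0.3 | 25% | 9% |
| 31 | one third | 0.3 | 11% | 7% |
| 31 | half | 0.5 | 9% | 3% |

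In the 10-component settings the unconstrained sum was significant in 3% to 8% of runs.

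**The case against.** The strongest reply is that the article does not commit to a single one-direction fit. Paired positive and negative fits, or a two-index model, are also WQS regression, and a condensed article may leave such settings to the full plan. That stands as far as it goes: a reader might infer that only one direction will be fitted and half the active components lost, but the text does not say so. It does fix the target, however. Even paired fits give two partial associations, and neither is the overall joint association that WQS is asked to deliver.

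A reader might also infer that the background sets vitamin D, magnesium and zinc against iron for the same outcomes throughout. It does not. The stated overlap is glucose metabolism only, and the Introduction itself describes the evidence as mixed. One clear domain, plus components of unknown direction, is enough to rule out assuming a single direction. It is not enough to say that every outcome is affected.

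Other planned analyses help. Single-exposure mixed models give each micronutrient a signed estimate, so opposing components would be visible. BKMR has no direction constraint, but its stated job is non-linearity and interactions, so the overall effect is not assigned to it. Training-validation splits address stability, not direction; the simulations used one and the effect remained.

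Finally, rates above 90% need large effects: 0.225 per step is 3 × 0.225 = 0.675 SD from lowest to highest quartile. That objection stands, and only the whole range should be cited.

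**Conclusion.** The mismatch between method and stated target is real, and its severity is moderate. With opposing components a standard WQS index gives a direction-specific part, and the Introduction makes opposition plausible for glucose metabolism at least. With zero net effect, the chance that a one-direction index is significant ran from near nominal (about 3% to 12%) to over 90%, depending on effect size, number of components and correlation. None of these inputs comes from the article, and rows were treated as independent, so the figures show the mechanism and do not predict the study's results.

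It would be too strong to say that WQS can never approximate the joint association. With correlated components of one sign it gave 0.62 against a true 0.60. The declared exploratory status of mixture results limits the consequences but does not align the estimator with its target.

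**What to change.** In section 2.10:
- Assign the net joint association to an estimator without a direction constraint, for example quantile g-computation with inference clustered by participant. Report the BKMR overall effect as a check.
- Keep WQS, with positive and negative indices for each outcome. State what each direction means for that outcome, since LDL and HDL cholesterol are both primary and have opposite risk meanings.
- Label the WQS results as direction-specific partial associations, and rank contributors within direction.

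If the full plan already specifies paired or two-index WQS, only the first and last items are needed. The cost is wording, a little more analysis with standard software, and somewhat wider intervals if all components do act in one direction. The analyses are described in the future tense, so the change can still be prespecified.

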## Discussion

3

Cardiometabolic diseases, including cardiovascular diseases and diabetes, remain major contributors to morbidity and mortality worldwide. These conditions arise from complex interactions among environmental exposures, lifestyle factors, aging-related physiological changes, and genetic susceptibility. Micronutrients participate in diverse physiological processes, including oxidative stress regulation, inflammatory response modulation, and metabolic homeostasis. Imbalances in micronutrient status may therefore be associated with cardiometabolic risk, particularly among middle-aged and older adults. Recent advances in multi-omics technologies provide opportunities to explore candidate biomarkers and potential biological pathways linking biomarker-based micronutrient profiles with cardiometabolic health.

This study protocol describes a longitudinal platform for assessing biomarker-based micronutrient profiles, conventional CRFs, secondary functional and biochemical biomarkers, and exploratory multi-omics features across four seasonal visits. The repeated-measure design may help characterize temporal variations in micronutrient profiles and their associations with cardiometabolic risk indicators. However, because this is an observational protocol, the planned analyses will be interpreted as exploratory and hypothesis-generating, and causal inference will remain limited. The planned integration of multi-omics data with environmental and lifestyle factors, such as physical activity, dietary quality, and socioeconomic status, may support a broader exploration of the determinants of cardiometabolic risk among middle-aged and older adults.

Future studies should further evaluate less-studied micronutrients, such as vanadium and molybdenum, and validate candidate biomarkers or pathways identified from exploratory analyses. Larger independent cohorts and, where appropriate, intervention studies will be needed to confirm whether micronutrient-related strategies can contribute to cardiometabolic disease prevention.

The main strengths of this exploratory panel study include its longitudinal design with short follow-up intervals, repeated measurements of exposures and outcomes, and biospecimen collection across four seasonal visits, which may improve the characterization of temporal variability in micronutrient profiles and cardiometabolic indicators. However, several limitations should also be noted. First, this study could not establish causality between exposure and outcomes. Second, the generalizability of the study should be interpreted with caution. The study population consists of community-dwelling middle-aged and older adults from Hefeng County. The study site was selected according to the research objective because of its distinctive mineral geochemical background, which may limit direct extrapolation to populations living in regions with different environmental, dietary, and trace-element exposure patterns. In addition, community-based volunteer recruitment and attrition during repeated visits may introduce selection bias. Therefore, the findings should not be interpreted as nationally representative estimates for all middle-aged and older adults or all populations at cardiometabolic risk. Third, although biomarker-based micronutrient profiles were used as the primary exposure indicators in this study, the influence of other unmeasured environmental chemicals or co-exposures with similar sources cannot be fully excluded, which may lead to residual confounding.
